**Sociodemographic, psychosocial, and behavioral correlates**						
	Demographic information (age in years, race or ethnicity, legal history, etc)	✓			✓	
	Health care use	✓			✓	
	Medical mistrust: Health Care System Distrust Scale	✓			✓	
	HIV knowledge or attitudes or risk: HIV-related knowledge scale, HIV-related attitudes scale, HIV stigma scale	✓			✓	
	PrEP knowledge or attitudes: willingness, intentions to use, barriers, stigma or conspiracy beliefs	✓			✓	
	Substance use: Alcohol use Disorders Identification Test, Texas Christian University Drug Screen V, Internalized Stigma of Substance Abuse	✓			✓	
	Psychiatric symptoms: Global Appraisal of Individual Needs-Short Screener	✓			✓	

^a^PrEP: pre-exposure prophylaxis.

#### Data Management and Analysis

REDCap will facilitate routine data checking and exportation of data for analysis. Analyses will be conducted using SAS (version 9.4; SAS Institute). Preliminary analyses will include the examination of descriptive statistics, distributions, and internal consistency reliability of scaled measures. Logistic regression will be used to examine the relationship between the condition and the primary outcomes (services linkage, ie, PrEP, substance use treatment), and all other dichotomous outcomes (eg, acceptance of PrEP and substance use treatment referral). Dependent variables in initial analyses will be summary dichotomous indicators based on both month 1 and 3 assessments, reflecting whether the outcome ever occurred. Subsequent analyses will separately examine whether outcomes occurred by month 1 and by month 3. Generalized linear models will be used to examine variously distributed continuous outcomes (navigator contacts, time-to-service linkage, and satisfaction). Exploratory analyses will build on these models to preliminarily examine the impact of potential moderating variables including sociodemographic characteristics, HIV risk behaviors and perceptions, PrEP-related knowledge and attitudes, substance use treatment behaviors, psychiatric symptoms, social support, and substance use on primary and secondary outcomes.

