### Aim 1: Development Phase

#### Participants

We present eligibility criteria by separate participant population. CLI-YAs (ages 18-29 years; n=24) will be eligible if they self-report recent CLI (past year); self-identify as HIV negative; endorse behaviors in the past 6 months indicating consideration of PrEP per the Center for Disease Control and Prevention’s risk indices [44]; meet the Tobacco, Alcohol, Prescription medication, and other Substance use Tools’ criteria for identifying the Diagnostic and Statistical Manual of Mental Disorders SUD (ie, ≥2 for tobacco, alcohol, and marijuana, and ≥1 for other substances) [45]; and are conversant in English. Exclusion criteria include being on PrEP, cognitive delays that would interfere with consent or participation, or inability to provide contact information for ≥2 locator individuals. CL system partners (n=2) will be in probation administration or frontline staff (eg, probation officers). Medical or public health system partners (n=2) will be involved in substance use treatment delivery and PrEP participant care in a setting where CLI participants are referred and will include individuals who have had experience navigating CLI to health services.

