### Aim 3: Pilot Randomized Controlled Trial Phase

#### Participants

To assess the feasibility, acceptability, and impact of the adapted eHealth-enhanced intervention for CLI-YAs, we will test the intervention in a randomized pilot trial with CLI-YAs (n=75).

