#### Recruitment and Randomization

Recruitment procedures will be informed by aim 2 results. Participants will be randomized either to the intervention group (n=50) or the standard of care (n=25) using a 2:1 randomization allocation scheme (Figure 2). Figure 3 provides a schematic of our study processes. Each participant will complete a baseline assessment immediately following the consent process. At the end of the baseline assessment, participants will be randomized to the intervention or control condition using a computerized algorithm programmed into REDCap (Research Electronic Data Capture; Vanderbilt University). Randomization will be blocked to avoid “runs” of assignment to the same.

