#### Standard of Care

The standard of care is a referral to substance use treatment and HIV prevention services from an individual’s case worker.

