#### Pilot Trial Outcomes

Primary outcomes are linkage to substance use treatment and PrEP services. Because PrEP and substance use treatment health service linkage are a process and not a 1-time event, we will also explore prelinkage (eg, navigator satisfaction) and downstream outcomes (eg, PrEP initiation, adherence, and substance use treatment continuing of care) in an exploratory fashion [55]. The navigator will track these outcomes, but the primary outcomes of (1) PrEP linkage will be attendance at a PrEP services appointment, verified by medical records and (2) substance use treatment linkage will be attendance at a substance use treatment appointment, verified by the navigator and medical provider collateral (if the participant agrees). Other exploratory outcomes include time to health service linkage (substance use and PrEP) and data on HIV testing at the PrEP linkage appointment (uptake, result). Participants will be asked whether and for how long they have experienced hospitalization, residential treatment, and detention since the intervention to account for any system barriers to linkage. We will also assess preferred methods for communicating with the navigator as well as participant satisfaction with the intervention and navigator services. Table 1 provides additional detail on outcomes and correlates.

**Table 1 table1:** Description and schedule of outcomes from a 90-day randomized controlled trial designed to link young adults impacted by the criminal legal system to substance use and HIV prevention services in Allegheny County, PA.

Primary outcomes		Baseline		30 days		90 days
PrEP^a^ linkage: medical record				✓		✓
Substance use treatment linkage: self-report, medical provider collateral if the participant agrees				✓		✓

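### With 25 controls, logistic regression as the only named method for the binary outcomes leaves no finite odds ratio if no control links to PrEP; name a penalised fit in advance

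*Protocol article*

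**What the plan says.** Aim 3 allocates as follows: "Participants will be randomized either to the intervention group (n=50) or the standard of care (n=25) using a 2:1 randomization allocation scheme". One of the two primary outcomes is defined so: "PrEP linkage will be attendance at a PrEP services appointment, verified by medical records". The comparator is described in one sentence: "The standard of care is a referral to substance use treatment and HIV prevention services from an individual’s case worker".

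Under Data Management and Analysis for aim 3, the method for both primaries is "Logistic regression will be used to examine the relationship between the condition and the primary outcomes (services linkage, ie, PrEP, substance use treatment"), and the same sentence extends it to every other dichotomous outcome. The main dependent variable is linkage at any time: "Dependent variables in initial analyses will be summary dichotomous indicators based on both month 1 and 3 assessments, reflecting whether the outcome ever occurred". The models are then repeated: "Subsequent analyses will separately examine whether outcomes occurred by month 1 and by month 3". Exploratory moderator analyses build on the same models. The software is SAS 9.4. The article names no penalised or exact method and no procedure for an empty cell, and it gives no expected linkage rate for either arm.

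**The concern.** A single method is fixed for every binary outcome while one arm has only 25 people. The Introduction describes low PrEP uptake and many barriers to access in this population, and controls receive a case-worker referral without navigation, so a small number of control linkages is conceivable. If that number is zero, the control log-odds has no finite maximum-likelihood estimate and neither does the odds ratio. This can happen when navigation works and usual care does not, so the default output could show a Wald p-value near 1 in the situation where the arms differ most. The pilot is meant to inform a larger trial, for which an unusable effect estimate on one of two primaries is a poor starting point. A rescue method chosen after seeing the empty cell would be data-driven.

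**Working it through.** **Inputs from the protocol article.** Total 75, allocated 2:1: 75 × 2/3 = 50 and 75 × 1/3 = 25, which agrees with the stated arm sizes. The outcome is binary (ever linked) and the method is logistic regression. The article states no power, alpha, effect size or control rate, so there is no figure of its own to reproduce. All linkage rates and event counts below are assumptions.

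**Step 1. Chance of an empty control cell.** P(0 of 25) = (1 − p)^25.

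| Assumed control rate p | P(0 of 25) |
|---|---|
| 1% | 0.78 |
| 2% | 0.60 |
| 5% | 0.28 |
| 10% | 0.07 |
| 15% | 0.017 |
| 20% | 0.004 |

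The chance passes one half only if p is below 1 − 0.5^(1/25) = 2.7%. It is under 10% once p exceeds 1 − 0.1^(1/25) = 8.8%. If 5 controls were lost, leaving 20 (also an assumption), (1 − p)^20 is 0.67, 0.36 and 0.12 at 2%, 5% and 10%.

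**Step 2. What the ordinary fit does.** The maximum-likelihood odds ratio is ad/(bc), where a and b are linked and not linked among the 50, and c and d the same among the 25. With c = 0 it is infinite. Fits of 5/50, 10/50 and 15/50 against 0/25 did not converge: the odds ratio diverged, the Wald interval ran from 0 to infinity and the Wald p-value was about 1.0.

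With c above zero the fit works but is wide. For 10/50 against:
- 1/25: (10 × 24)/(40 × 1) = 6.0, 95% interval 0.72 to 49.8
- 2/25: (10 × 23)/(40 × 2) = 2.88, interval 0.58 to 14.3
- 3/25: (10 × 22)/(40 × 3) = 1.83, interval 0.46 to 7.4

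So only an empty (or full) cell causes breakdown.

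**Step 3. What other methods give with 10/50 against 0/25.** The likelihood-ratio statistic is 2 × [(10 ln 0.2 + 40 ln 0.8) + 0 − (10 ln(10/75) + 65 ln(65/75))] = 2 × (−25.02 + 29.45) = 8.86, p = 0.003. Fisher's exact test gives p = 0.025. For one binary covariate the Firth estimate equals adding 0.5 to each cell: (10.5 × 25.5)/(40.5 × 0.5) = 13.2. Its profile penalised-likelihood 95% interval is about 1.6 to 1,700. The simple Wald interval around the same estimate is 0.74 to 236, which includes 1, so the type of interval matters as well as the penalty.

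**Step 4. The further models.** Linkages by month 1 cannot exceed linkages at any time, so an empty cell is at least as probable there. For a binary moderator that splits the controls 12 and 13 (an assumption), P(at least one empty control subgroup) = 1 − [1 − (1 − p)^12][1 − (1 − p)^13]. At 5%: 1 − (1 − 0.540)(1 − 0.513) = 0.78. At 10%: 1 − (1 − 0.282)(1 − 0.254) = 0.46. At 20%: 1 − (1 − 0.069)(1 − 0.055) = 0.12. With an empty subgroup the treatment-by-moderator interaction has no finite maximum-likelihood estimate.

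**The case against.** The strongest objection is that the article says logistic regression and no more. Firth and exact estimation are also logistic regression, both are available in the named software, and estimator details are commonly left to a full protocol or analysis plan that is not shown. That stands in part: the silence is not itself an error, and a fuller plan may already cover this. But an unqualified reference to logistic regression normally means maximum likelihood, and the article fixes it as the one method for all binary outcomes at a stated control size where that fit can break down.

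A reader might go further and infer that the model will fail whenever few controls link, or that failure is likely. The documents support neither. One to three control events give finite estimates. No control rate is stated, and the chance of 0/25 is below 2% at an assumed rate of 15%. Three further facts weigh against assuming a very low rate. Controls do receive a referral to HIV prevention services. The outcome is attending an appointment, not starting PrEP. The low uptake described in the Introduction concerns PrEP use and comes without an attendance rate. Nor can controls be called PrEP-naive: "Exclusion criteria include being on PrEP" refers to current use, it belongs to the aim 1 criteria, and the criteria for aims 2 and 3 are still to be settled.

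It is also fair that the pilot would not be left with nothing. Arm proportions and the likelihood-ratio test survive an empty cell, no stated decision rule depends on a Wald interval, the moderator models are exploratory, and much of the imprecision comes from having 25 controls whatever the estimator.

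**Conclusion.** The point holds as a matter of robustness, not as a demonstrated flaw. If no control links to PrEP, the ordinary fit gives no usable odds ratio, Wald test or Wald interval for one of the two primaries. The chance is 60%, 28%, 7% and 0.4% at assumed control rates of 2%, 5%, 10% and 20%. That makes it plausible at low rates; with no rate in the article, it cannot be called likely. The month-1 and moderator analyses are more exposed, with 78% and 46% chances of an empty control subgroup at 5% and 10% under the assumed 12/13 split. These figures treat participants as independent with a common control rate and, except where stated, assume all 25 controls are followed. The remedy is cheap enough that the analysis should be specified this way before data are seen.

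**What to change.** In the aim 3 Data Management and Analysis section, specify that binary outcomes are analysed by Firth-penalised logistic regression with profile-likelihood 95% intervals. This applies to the primaries, the month-1 and month-3 repeats and the moderator models. Add that the proportion linked in each arm and the risk difference with a score (Miettinen-Nurminen) 95% interval are reported alongside the odds ratio. The risk difference is a companion here; making it the main effect measure would be a matter of preference.

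In SAS 9.4 these are the FIRTH and CLODDS=PL options of PROC LOGISTIC and RISKDIFF(CL=MN) in PROC FREQ. The cost is slight shrinkage of the odds ratio (for 10/50 against 1/25, from 6.0 to 4.2) and one more line of output. Sample size and data collection do not change. The penalty keeps the estimate finite but does not make it precise: intervals will stay wide with 25 controls.

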#### Data Collection

The baseline assessment will occur immediately following participant consent, prior to randomization, and follow-up assessments will occur at 1 month and 3 months (Figure 3). Data will be collected via face-to-face one-on-one interviews in private locations to ensure confidentiality. If face-to-face interviews are not possible, a participant will be given the option of completing the assessment via a secure web-based survey link. Regardless of the method of interview administration, REDCap will be used to collect data (ie, in person on tablets or via a secure REDCap survey sent via email). If completing the assessment via a secure link, specific instructions will be provided to the participant to inform them about how to keep their data private.

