#### Exit Interviews

We will conduct exit interviews with a subsample of intervention arm participants (n=10), the navigator (n=1), and partners from participating systems (n=4). Interviews will assess intervention acceptability and suggestions for improvement. To recruit for qualitative exit interviews, a member of the study team will contact intervention participants to invite them to a phone interview (~30 minutes). To ensure a range of responses, we will sample for (1) participants who connect or did not connect to the navigator and who linked or did not link to PrEP and substance use treatment services and (2) variation in characteristics that may impact the intervention (eg, psychiatric symptoms). We will seek to understand reasons why the intervention was or was not successful for a particular participant (via participant and navigator report). To analyze exit interview data, we will mirror aim 2’s rapid qualitative analysis processes.

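### Time to service linkage is right-censored, but the article models it as an ordinary continuous outcome in a generalized linear model, with no place for participants who never link

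*Protocol article*

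**What the plan says.** Under Aim 3, Data Management and Analysis, the article assigns a model to three outcomes together: "Generalized linear models will be used to examine variously distributed continuous outcomes (navigator contacts, time-to-service linkage, and satisfaction". Pilot Trial Outcomes gives the status of this one: "Other exploratory outcomes include time to health service linkage (substance use and PrEP", so it is exploratory and covers two services. The events are defined in the same section: "PrEP linkage will be attendance at a PrEP services appointment, verified by medical records", and "substance use treatment linkage will be attendance at a substance use treatment appointment". Under Data Collection, "follow-up assessments will occur at 1 month and 3 months".

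The article expects some participants never to link. The primary dependent variables are "summary dichotomous indicators based on both month 1 and 3 assessments, reflecting whether the outcome ever occurred", and the Aim 3 exit interviews will sample participants "who linked or did not link to PrEP and substance use treatment services". The trial size is fixed under Recruitment and Randomization: "Participants will be randomized either to the intervention group (n=50) or the standard of care (n=25) using a 2:1 randomization allocation scheme". The article does not mention censoring, a survival method, or a value to be given to someone who does not link.

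**The concern.** Navigator contacts and satisfaction are not censored by a failure to link. Time to linkage is: for a non-linker, all that is known is that it exceeds the time under observation. A generalized linear model for a continuous response needs a number for each participant it includes. Used as described, it would be fitted only to those who linked.

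That comparison is no longer between the randomised groups. Linkage happens after randomisation, and raising it is the purpose of the intervention. If navigation brings in people who are harder to reach and who link later, the intervention arm can look slower because it succeeded. The article says that the pilot will inform a larger trial and that the moderator analyses will build on these same models, so a misleading sign could be carried forward.

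**Working it through.** **Inputs from the article.** 75 participants, 75 × 2/3 = 50 intervention and 75 × 1/3 = 25 standard of care; follow-up to T = 90 days. The article states no power calculation, so there is none to reproduce.

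**Assumptions.** The article gives no linkage rates. The 90-day proportion linked, p, is taken as 10% to 30% on standard of care and 30% to 60% on intervention. The hazard is constant, there is no dropout, and tests are two-sided at 5%.

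**Formulas.** Hazard λ = −ln(1 − p)/T. Mean time among linkers = 1/λ − T(1 − p)/p. Restricted mean time to day 90, over all participants = p/λ.

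**Worked case, 50% v 20%.**
- Intervention: 1/λ = 90/0.6931 = 129.8 days. Control: 1/λ = 90/0.2231 = 403.3 days. Hazard ratio 0.6931/0.2231 = 3.1.
- Observed times: 50 × 0.5 = 25 and 25 × 0.2 = 5. The other 75 − 30 = 45 participants have none.
- Mean among linkers: 129.8 − 90 = 39.8 days v 403.3 − 360 = 43.3 days, a difference of 3.5 days.
- Restricted mean, all 75: 0.5 × 129.8 = 64.9 days v 0.2 × 403.3 = 80.7 days, a difference of about 15.7 days.

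**Simulated power (2,000 or 3,000 trials per run).** Ranges cover separate runs; the linkers-only comparison was a t-test, a Gamma log-link model, or both. The last column sets non-linkers to day 90.

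| Linked, intervention v control | Hazard ratio | Expected linkers | Linkers only | Log-rank, all 75 | Day 90 for non-linkers, all 75 |
|---|---|---|---|---|---|
| 30% v 10% | 3.4 | 15 v 2.5 | 0.04–0.08 | 0.47–0.51 | 0.54 |
| 40% v 10% | 4.8 | 20 v 2.5 | 0.04 | 0.80–0.81 | 0.78 |
| 40% v 20% | 2.3 | 20 v 5 | 0.05–0.06 | 0.39–0.40 | 0.40 |
| 50% v 20% | 3.1 | 25 v 5 | 0.05–0.06 | 0.70–0.74 | 0.70 |
| 60% v 30% | 2.6 | 30 v 7.5 | 0.05 | 0.68 | not run |

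At 50% v 20%, the intervention appears slower in about 39% of trials with linkers only, and in about 1% with day 90 assigned. At 40% v 10%, an arm has fewer than two linkers in 27% to 28% of trials.

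**Late-linker pattern (constructed).** Suppose 20% in each arm link at mean day 15, and the intervention adds 30% who link at mean day 45.
- Linker means: (0.2 × 15 + 0.3 × 45)/0.5 = 33 days v 15 days, the wrong sign.
- Means over all participants, with non-linkers at day 90: 3 + 13.5 + 45 = 61.5 days v 3 + 72 = 75 days, the right sign.

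A simulated variant had 20% in each arm linking by day 30 and a further 30% of the intervention arm linking between days 30 and 90. The linkers-only mean was about 27 days longer with the intervention, and the Gamma model was significant in the wrong direction in about 90% of trials.

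**The case against.** A reader might infer that the plan restricts the comparison to linkers. It does not say so. That is the natural consequence of the stated model, and the linkers-only figures above depend on it.

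The strongest reply is that the model can be kept by giving non-linkers the value 90. Day 90 is the end of follow-up, so the value is not arbitrary. With complete follow-up, a comparison of mean min(time, 90) over all 75 estimates the difference in restricted mean time, which is a sound analysis. The simulation bears this out: power is close to log-rank, the wrong sign is rare, and type I error was 0.05 with 30% linked in both arms. This part of the objection stands. It fails for participants lost before day 90, whose time must still be censored. Completeness is harder to count on for substance use treatment, where provider confirmation depends on the participant's agreement.

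It can also be said that such handling rules belong in an analysis plan that is not shown. That would answer a complaint about missing detail. Here the article names both a model and an outcome type, and neither fits a censored time. Piecewise-exponential or discrete-time models can be fitted as generalized linear models, but their response is an event count or indicator, not a continuous time.

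Finally, the outcome is exploratory and does not appear in Table 1. The separate analyses of linkage by month 1 and by month 3 would show part of the timing correctly. These points limit the severity but do not remove the mismatch.

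**Conclusion.** The point holds, at moderate severity. The article treats a right-censored time as an ordinary continuous outcome and makes no provision for participants who do not link or are lost early. Read at face value, this leaves a comparison among linkers with power near its false-positive rate (0.04 to 0.08 across the scenarios, against 0.39 to 0.81 for log-rank), and the direction of effect can reverse.

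These sizes rest on assumed linkage rates, constant hazards and no dropout, and on non-linkers being dropped. The late-linker reversal is an illustration, not a prediction. The documents do not support the stronger reading that the trial's main comparison is compromised. The primary logistic regression keeps non-linkers as not linked, and the article states no decision rule or sample size that depends on time to linkage.

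**What to change.** Remove time-to-service linkage from the generalized linear model list and replace it with one sentence. Days from randomisation to first attended appointment will be analysed in all randomised participants, separately for PrEP and for substance use treatment, censored at day 90 or last ascertainment. Use Kaplan-Meier curves by arm with a log-rank test or a Cox model (Firth-penalised if events are sparse), or the difference in restricted mean time to day 90.

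The cost is that sentence and a little more analysis in the planned SAS 9.4. No new outcome is needed, because any analysis of time to linkage already requires the appointment dates. The last date on which linkage status was known must be recorded for anyone lost before day 90.
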